In addition, several secondary outcomes will be analysed: utilisation of hospital emergency department, emergency outpatient care, and non-emergency outpatient care, as well as the place of discharge. These outcomes were chosen to gain a more comprehensive understanding of the entire patient pathway in relation to the treatment provided at each STATAMED ward. They are also relevant for assessing the cost-effectiveness of STATAMED.

We propose three additional hypotheses regarding the impact of STATAMED on secondary outcomes:Reduction in hospital emergency admissions and utilisation of emergency outpatient care: We hypothesise that STATAMED will reduce hospital emergency admissions and the utilisation of emergency outpatient care after initial discharge through improved coordination and the provision of follow-up care. This hypothesis is supported by findings from a systematic review by Raven et al. [32], which suggest that case management interventions can reduce emergency department visits.Non-emergency outpatient care utilisation: We expect two opposing effects on non-emergency outpatient care utilisation. Follow-up care provided by the mobile nurse may substitute for certain outpatient services, whereas the coordination of follow-up care by the case manager, including scheduling appointments with outpatient physicians, is expected to increase the utilisation of non-emergency outpatient care.Increase in discharges to home rather than nursing care facilities: We also hypothesise that patients treated at STATAMED wards will be more likely to be discharged to their homes rather than to nursing care facilities. This is attributed to improved treatment quality, which is expected to prevent overtreatment and reduce the risk of nosocomial and other complications.

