#### Exclusion criteria for patients

Patients will be excluded if they meet any of the following criteria: They require highly technical diagnostic procedures (as defined by the eligibility criteria for STATAMED wards), require inpatient surgery, or have been transferred from other hospitals.

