#### Eligibility criteria for referring entities

Referring entities, including GPs, office-based specialists, nursing homes, ambulatory care services, and emergency services, must complete mandatory training on STATAMED-specific processes, such as the case review process, prior to participation. Additionally, they must sign a participation agreement to be authorised to refer patients to STATAMED wards.

Participation is voluntary and may be discontinued at any time. Referring entities that choose to withdraw from the project may cease referring patients to STATAMED wards without further consequences. They may also revoke consent for the use of their practice-related data in the scientific evaluation, in accordance with applicable data protection regulations. In the event of withdrawal, the health insurer leading the project consortium should be notified to ensure accurate documentation and appropriate adjustments to recruitment planning.

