### Intervention description {11a}

STATAMED encompasses a range of interventions designed to ensure continuity of care and improve coordination between hospital and outpatient settings both before and after hospital discharge. The following interventions will be implemented:Short-stay ward: Each participating hospital site will include (or, in the case of very small hospitals, consist of) a dedicated short-stay ward (“STATAMED ward”) for patients with general medical conditions who require inpatient treatment, have a diagnosis matching a STATAMED-specific ICD-10 code, and are expected to have an uncomplicated disease course (see eligibility criteria {10}). The average length of stay in a STATAMED ward is anticipated to be approximately 3 days.Case review: To determine whether a patient is suitable for treatment in a STATAMED ward, a mandatory case review will be conducted between the referring physician and the lead STATAMED physician of the respective STATAMED ward. During this review, diagnoses will be assessed and discussed, eligibility will be confirmed, and a treatment plan will be collaboratively developed. If the lead STATAMED physician approves the admission, a planned admission will be scheduled, specifying the date and time to ensure that the STATAMED ward can prepare for the patient’s arrival and admit him or her without delay.Case manager: Case managers in each STATAMED ward will coordinate interdisciplinary and cross-sectoral treatment planning for the post-discharge period. During the hospital stay, they will participate in medical rounds to support discharge planning. Their responsibilities include assisting patients with urgent social care needs, such as arranging home care services, procuring assistive devices, and securing short-term care home placements. After discharge, case managers will help coordinate necessary therapeutic measures, including organising nursing services, scheduling physiotherapy sessions, arranging home visits by occupational therapists, and making appointments with outpatient physicians. They will also communicate with and involve the patient’s caregivers and relatives as needed. Case managers hold a basic qualification in a medical, therapeutic, nursing, or social care profession (e.g. medical assistants) and have received project-specific training to prepare them for their tasks in the STATAMED trial.Mobile nurses: These nurses will provide follow-up care either at the patient’s home or in a long-term care facility. Their responsibilities include medical tasks such as monitoring vital signs, collecting blood samples for analysis, and performing ultrasounds or electrocardiograms. They also assess patients for functional deficits, provide fall prevention guidance, and report on follow-up care needs. Additionally, mobile nurses can assist with the admission process. If a patient’s regular referring physician is unavailable, the mobile nurse can visit the patient before admission to assess their condition. In such cases, the lead STATAMED physician will be consulted via telemedicine to make the admission decision, and the mandatory referral case review will take place at a later date.

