### Outcomes {12}

All outcomes will be measured using claims data from the participating statutory health insurers. A detailed description of the claims data is provided below (see “Plans for assessment and collection of outcomes {18a}”).

The combined primary outcome consists of the following:

(1) Length of hospital stay, which is measured in days and calculated as the difference between the admission date and discharge date. (2) A 30-day hospital readmission rate, which captures the number and length of hospital stays within 30 days after discharge

The secondary outcomes are as follows:Utilisation of hospital emergency departmentsUtilisation of emergency outpatient careUtilisation of nonemergency outpatient carePlace of discharge (discharge to patient home vs. discharge to a care facility)

Utilisation of hospital emergency departments, utilisation of emergency outpatient care, and utilisation of nonemergency outpatient care will be measured in monetary terms and by the number of services provided. These outcomes will be measured before and after the hospital stay.

A health economic evaluation will also be conducted to assess the cost-effectiveness of STATAMED.

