### Statistical methods

#### Statistical methods for primary and secondary outcomes {20a}

The two co-primary outcomes (length of hospital stay, 30-day hospital readmission rate) are treated as continuous variables. The secondary outcomes (utilisation of hospital emergency departments, emergency outpatient care, and nonemergency outpatient care, as well as place of discharge) are also continuous except for the place of discharge (home, care facility, other), which is categorial.

Because there are two co-primary outcomes without hierarchical ordering, a correction for multiple testing is required. A Bonferroni correction will be applied, resulting in a one-sided significance level of α/2 = 2.5% for each primary outcome given a global type I error rate of *α* = 5%. However, the Bonferroni method is known to be conservative. As an alternative, the Romano-Wolf procedure [43] may be used, as it more efficiently controls the family-wise error rate by accounting for the dependence structure among outcomes through resampling (see “Sample size {14}”).

When analysing stepped-wedge designs, it is important to account for temporal effects given that each cluster transitions to the intervention in a stepwise fashion. In this study, this is particularly important because the STATAMED wards will gain experience with implementing the intervention over time. Additionally, the longitudinal design of the study necessitates the consideration of calendar time because patient case mix may vary by season (e.g. winter versus summer) due to the focus of the study on general medical conditions. To account for these temporal effects, generalised linear mixed models (GLMMs) and generalised estimating equations (GEEs) will be applied [45–47]. Propensity score matching, considering age, gender, and morbidity, will be used to ensure comparability between the control and intervention groups.

To avoid bias from patients who are transferred to other hospitals during STATAMED treatment or those who meet eligibility criteria but prefer to be treated at a non-STATAMED hospital, the analysis will be conducted according to the intention-to-treat and per-protocol principles [48].

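### Place of discharge ignores where the patient lived before admission, so nursing-home residents dilute the secondary outcome and, if unevenly distributed, bias it

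*Protocol article*

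**What the plan says.** Outcomes {12} gives place of discharge two destinations: "discharge to patient home vs. discharge to a care facility". Statistical methods {20a} gives it three: "place of discharge (home, care facility, other), which is categorial". Neither section refers to residence before admission. Measurement both before and after the stay is stated in Outcomes {12} only for the three utilisation outcomes.

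The hypothesis in Objectives {7} is directional: patients on STATAMED wards are expected to be "more likely to be discharged to their homes rather than to nursing care facilities". The reason given is better treatment, with less overtreatment and fewer complications.

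Residents of care facilities can enter the trial. The list of referrers reads "Referring entities, including GPs, office-based specialists, nursing homes, ambulatory care services, and emergency services". The exclusion criteria are a need for highly technical diagnostics and patients who "require inpatient surgery, or have been transferred from other hospitals"; living in a care facility is not among them.

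On adjustment, Statistical methods {20a} says "Propensity score matching, considering age, gender, and morbidity, will be used to ensure comparability between the control and intervention groups". Place of residence appears only in the section on additional analyses {20b}, as a subgroup characteristic, and it is not defined there as care-facility status.

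**The concern.** A nursing-home resident who recovers normally is discharged back to the nursing home. If that counts as a care-facility discharge, a good result is scored in the unfavourable category whatever the ward did. The proposed mechanism, fewer complications and hence fewer placements, cannot change the result for such a patient.

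Two consequences follow. First, residents add the same fixed block of care-facility discharges to both groups, which shrinks the visible contrast even when their shares are equal. Second, if the shares differ, the outcome partly measures who was admitted and not what the care achieved. Matching on age, gender and morbidity need not remove such a difference, because two patients alike on all three can live at home and in a nursing home respectively. At stake is the interpretation of one secondary outcome and its hypothesis.

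**Working it through.** **How a returning resident is classified.** There is no explicit rule, so the wording has to be read. Intervention description {11a} has the mobile nurse providing "follow-up care either at the patient’s home or in a long-term care facility", and Participant timeline {13} draws the same contrast. These sentences describe visits and not outcome coding, but they show that the article does not use home to include a care facility. On that usage, a returning resident falls under care facility.

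**Inputs.** The documents give no rate, effect size or power for this outcome, so there is no stated figure to reproduce. All values below are assumptions:
- r: share of patients already living in a care facility at admission, all assumed to return there
- q: risk of new placement among patients admitted from home
- Subscripts C and T: control and STATAMED

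**Formula.** Observed care-facility discharge = r + (1 − r)q.

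**Dilution with equal shares**, q_C = 5%, q_T = 4%:

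| r | Control | STATAMED | Relative reduction | Difference |
|---|---|---|---|---|
| 0% | 5.0% | 4.0% | 20% | 1.0 point |
| 10% | 0.10 + 0.90 × 0.05 = 14.5% | 0.10 + 0.90 × 0.04 = 13.6% | 1 − 13.6/14.5 = 6.2% | 0.9 point |
| 20% | 0.20 + 0.80 × 0.05 = 24.0% | 0.20 + 0.80 × 0.04 = 23.2% | 1 − 23.2/24.0 = 3.3% | 0.8 point |

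A second set of rates, 8.0% vs 6.4% (risk ratio 0.80), gives observed risk ratios of 0.92, 0.95 and 0.97 at r = 10%, 20% and 30%.

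**Bias with unequal shares and no true effect**, q = 5% in both groups. The spurious difference is (r_T − r_C)(1 − q). With r_C = 10%:
- r_T = 15%: 19.25% vs 14.5%, 4.75 points against STATAMED
- r_T = 5%: 0.05 + 0.95 × 0.05 = 9.75% vs 14.5%, 4.75 points in its favour

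**Imbalance that cancels a true effect.** Setting the two observed rates equal gives r_T = [r_C + (1 − r_C)q_C − q_T] / (1 − q_T). With r_C = 10%:
- 5% vs 4%: (0.145 − 0.04)/0.96 = 10.94%, an excess of 0.9 point
- 8.0% vs 6.4%: (0.172 − 0.064)/0.936 = 11.54%, an excess of 1.5 points

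For q_C from 5% to 10% with a 20% relative reduction, and r_C from 5% to 20%, the excess that cancels the effect runs from 0.8 to 2.1 points.

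**What restriction to home-dwelling patients does.** It recovers q_C vs q_T whatever r is. For illustration only, take 2076 patients per group at admission (the number that the sample size section gives for the primary outcome), 8.0% vs 6.4%, a two-sided 5% test and no clustering. At r = 10%, power is about 47% after restriction (2076 × 0.90 ≈ 1868 per group) and about 24% with residents counted. At r = 20% it is about 43% and 15%. Losing the residents costs less than keeping them.

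**The case against.** The strongest reply is that the article states category labels, not a coding rule. An analysis plan that is not shown could read patient home as usual residence, and the operational coding of a claims-based secondary outcome is often left to such a plan. The matching sentence is also a summary and lists no model covariates. This stands in part: it rules out saying that the trial will miscode residents. It does not remove the point, because the outcome definition, the directional hypothesis and the matching variables are all stated here, and as worded they do not fit together.

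A reader might go further and infer that STATAMED recruits specially through nursing homes, so that the bias must run against it and reverse the effect. The documents do not support that. Nursing homes are one of five referrer types, and the recruitment section singles none of them out. Control group 1 is defined by clusters formed from the same types of entity (Trial design {8}), which limits imbalance. It does not exclude it: STATAMED patients pass through participating referrers, case review and consent, while controls are found retrospectively by ICD-10 code. Those filters could raise or lower the resident share. Nor do mobile-nurse visits in care facilities prove prior residence, since they may follow new placements.

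The size also depends on scale. With equal shares the risk difference shrinks only by the factor 1 − r, a loss of 10% or 20% here. The ratio of home discharges does not change at all (96/95 and 86.4/85.5 are both 1.011). The large relative dilution belongs to the care-facility category.

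**Conclusion.** The point holds in a limited form. As worded, place of discharge takes no account of prior residence, and residents who return to their nursing home fall, on the plain reading, in the category that the hypothesis treats as unfavourable. With equal shares of 10% or 20%, a 20% relative reduction in new placements appears as about 6% or 3% (1.0 point becomes 0.9 or 0.8). With unequal shares the result is biased. Under the assumed rates a residual excess of residents of about 1 to 2 points in the STATAMED group would be enough to cancel the effect, and a deficit would exaggerate it.

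This rests on the plain reading of an unstated coding rule, on assumed rates throughout, on all residents returning to their facility and, for the bias, on an imbalance that survives matching. The documents show neither that such an imbalance exists nor its direction, so a claim that the effect will be reversed would go too far. The co-primary outcomes and the sample size are unaffected. It is worth correcting before the data are delivered, and it does not threaten the trial's main conclusion.

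**What to change.** 1. In Outcomes {12}, define the outcome as new discharge to a care facility among patients who lived at home before admission. Alternatively, keep all patients and code a return to the prior residence as no change.
2. Add care-facility residence before admission to the matching variables or the model covariates in Statistical methods {20a}, if the insurers can supply it.
3. Use the same categories in Outcomes {12} and Statistical methods {20a}, which now give two and three.

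The cost is a sentence in the outcome definition, one added covariate and one extra data item, requested before the preliminary delivery planned for about June 2026. That the insurers hold this item is an assumption: the examples in Table 1 do not name it, but they are only examples. Restriction leaves fewer patients in this one secondary outcome.

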**Fig. 1 Fig1:**
[figure not shown]
Study design

The intervention group consists of all eligible patients (see the “Eligibility criteria {10}”) treated in the STATAMED wards. Eligible individuals must be covered by one of the participating statutory health insurers and meet the eligibility criteria. Claims data will only be provided for individuals insured by one of the participating statutory health insurers.

Additionally, three control groups are planned:Control group 1 consists of patients who meet the eligibility criteria for treatment in a STATAMED ward but receive usual hospital care at a non-STATAMED hospital because their referring entity is located in a cluster assigned to the control phase at the time of treatment. This is the standard control group in the stepped-wedge design, enabling the analysis of each cluster before and after STATAMED is introduced.Control group 2 consists of patients who meet the eligibility criteria for treatment at a STATAMED ward and whose referring entity is located in a cluster assigned to the intervention phase at the time of treatment but who are referred to and receive treatment at a non-STATAMED hospital. This group allows for the examination of possible selection effects (i.e. patients who prefer usual hospital care over STATAMED).Control group 3 consists of patients who meet the eligibility criteria for treatment at a STATAMED ward but whose referring entity is located outside a participating hospital site’s catchment area, resulting in treatment at a non-STATAMED hospital. This group allows for the consideration of additional spatial effects. Figure 2 illustrates the various control groups.

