## Methods: participants, interventions, and outcomes

### Study setting {9}

STATAMED will be implemented at six hospital sites across Germany, with three located in rural areas and three in urban areas. The list of study sites can be found in the registry (DRKS00033096).

The six sites consist of small- and medium-sized hospitals, with the smallest having 15 beds and the largest 229 beds. The sites also vary in other characteristics, such as the number of wards present in addition to the STATAMED ward and whether the hospital has an emergency department. This information is available to the evaluators and will be taken into account during the analysis.

Data for the control group will be obtained from patients who receive treatment at non-STATAMED hospitals. These may be any hospital that is allowed to treat patients who are covered by statutory health insurance (see also “Explanation for the choice of comparators {6b}”).

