### Data collection and management

#### Plans for assessment and collection of outcome {18a}

Claims data from the statutory health insurers participating in the trial (AOK Rheinland-Hamburg and AOK Niedersachsen) will be used as the primary data source. Claims data are secondary data collected by health insurers for billing purposes and are considered reliable and valid. Because they reflect actual treatments provided by physicians and hospitals, they contribute to ensuring external validity. Matching methods will be applied in the analysis to improve comparability between the intervention and control groups, minimising selection bias [44].

To ensure data quality, data will be delivered at two time points by the participating health insurers. The final data delivery is expected at the end of the project period (approximately January 2027). Before this, a preliminary data delivery will take place (approximately June 2026) to check the completeness and plausibility of the data.

Although the outcomes will be measured using claims data, additional data will be collected to ensure the feasibility of the analysis. Table 1 provides an overview of the various data sources.

**Table 1 Tab1:** Data sources

Data set	Description	Utilisation
Claims data from participating statutory health insurers	Secondary data collected by statutory health insurers for billing purposes. The data set includes: patient master data (e.g., sex, year of birth, postal code), outpatient data (e.g., pseudonymised physician number, diagnoses[ICD codes], procedures, billed services), medicines (e.g., ATC code, issuance date, price/amount of reimbursement), inpatient data(e.g., hospital number, diagnoses [ICD-code], procedures, date of inpatient admission and duration of hospital stay, billed case rates)	Measuring primary andsecondary outcomes
Task documentation data	STATAMED-specific tasks performed by the lead STATAMED physician, mobile nurse, and case manager must be documented (e.g., mobile nurses document tasks performed during follow-up care, such as measuring vitalsigns or taking blood samples)	Allows assessment and comparison of implementationacross different STATAMED wards
Information on referring entity	Identification numbers and postal codes of referring entities	Allows assignment of patientlevel claims data to the correct cluster

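### Pre-stay utilisation is to be measured, but the stated matching set is age, gender and morbidity only, and no use of the pre-stay values is described

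*Protocol article*

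**What the plan says.** Outcomes {12} lists three utilisation outcomes (hospital emergency departments, emergency outpatient care, non-emergency outpatient care) that "will be measured in monetary terms and by the number of services provided", and adds: "These outcomes will be measured before and after the hospital stay".

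Statistical methods {20a} names the comparability variables: "Propensity score matching, considering age, gender, and morbidity, will be used to ensure comparability between the control and intervention groups". For the outcome models it says that "generalised linear mixed models (GLMMs) and generalised estimating equations (GEEs) will be applied", in order to handle temporal effects. It lists no patient-level covariates for them.

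Plans for assessment and collection of outcome {18a} gives the purpose of the matching: "Matching methods will be applied in the analysis to improve comparability between the intervention and control groups, minimising selection bias". Trial design {8} also recognises selection; of control group 2 it says: "This group allows for the examination of possible selection effects".

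No section says where the pre-stay utilisation values enter an analysis.

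**The concern.** The timing of each cluster's switch is randomised, but the intervention group is defined as the eligible patients actually treated in a STATAMED ward. They get there through a trained, voluntarily participating referring entity, a case review with the lead physician, and consent. Controls pass none of these filters and are identified afterwards from ICD-10 codes in claims. How closely a patient is tied to outpatient care, and how often that patient uses emergency care, could plausibly affect who takes the STATAMED route. The same behaviour is what the secondary outcomes measure after the stay, and the article has a directional hypothesis for emergency use.

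If matching on three variables leaves prior use unbalanced, part of that difference can show up as an intervention effect, and a larger sample would not remove it. Leaving a baseline value out of the outcome model also costs precision, to a degree that depends on how much it explains beyond the variables already used.

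**Working it through.** The article gives no correlation between pre-stay use and any outcome, so there is no plan figure to reproduce here. The numbers below rest on stated assumptions.

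**Step 1. What is fixed and what is open.**

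| Item | Stated | Pre-stay use included? |
|---|---|---|
| Measurement of the three utilisation outcomes | Before and after the stay | Yes, as data |
| Propensity score | Age, gender, morbidity | Not named |
| GLMM/GEE | Temporal effects; patient covariates not listed | Not stated either way |

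The omission is explicit for the propensity score only.

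**Step 2. Precision.** Let R² be the share of the remaining outcome variance that pre-stay use explains beyond age, gender and morbidity. When it is added to the outcome model, the variance factor is 1 − R² and the SE factor is √(1 − R²). The last column assumes 80% power beforehand at two-sided 0.05; the article states no power.

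| Assumed R² | Variance factor | SE factor | SE reduction | Power at the same N |
|---|---|---|---|---|
| 0.02 | 0.98 | 0.990 | 1.0% | about 81% |
| 0.05 | 0.95 | 0.975 | 2.5% | about 82% |
| 0.10 | 0.90 | 0.949 | 5.1% | about 84% |
| 0.25 | 0.75 | 0.866 | 13.4% | about 90% |

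To put this on the scale of the updated readmission sample size: if the increment for readmission were 0.02 to 0.10, 2076 would correspond to 2076 × 0.98 ≈ 2035 down to 2076 × 0.90 ≈ 1869. The pre-stay values are not baselines of readmission, so the lower end of that R² range is the safer guess.

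**Step 3. Bias.** A residual standardised difference d in prior use, with partial correlation r to the outcome, shifts the comparison by about d × r outcome SDs. With d = 0.1 and r = 0.2 to 0.3 (both assumed), the shift is 0.02 to 0.03 SD.

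For comparison, take readmission as a yes/no outcome. This is a simplification, since the article treats it as continuous. The 15% relative difference in Sample size {14}, at an assumed control rate p, equals 0.15p / √(p(1 − p)) SD:

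- p = 0.10: 0.015 / 0.30 = 0.050 SD
- p = 0.20: 0.030 / 0.40 = 0.075 SD

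The shift would then be 0.02 / 0.075 = 27% to 0.03 / 0.050 = 60% of the target effect. With the updated 20% effect the targets are 0.020 / 0.30 = 0.067 and 0.040 / 0.40 = 0.100 SD, and the shift is 0.02 / 0.100 = 20% to 0.03 / 0.067 = 45%. These figures show what a modest imbalance could do. They are not evidence that one exists.

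**Step 4. When the baseline stops being a baseline.** Participant timeline {13} puts admission about 1 to 2 days after the case review. Intervention description {11a} allows a mobile nurse to visit before admission. Use recorded in the last days before admission can therefore already be affected by the intervention, and adjusting for it could remove or distort part of the effect.

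**The case against.** The strongest reply is that this is detail for an analysis plan. The covariates of the GLMM/GEE are unlisted, not excluded, and measuring use before and after the stay may itself point to a baseline-adjusted or change analysis. The three matching variables are also not the whole adjustment set: of the site characteristics, Study setting {9} says "This information is available to the evaluators and will be taken into account during the analysis". Morbidity is undefined and, if built from claims, could already carry part of prior use. The intention-to-treat analysis is also meant to limit bias from patients who choose another hospital.

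Most of this stands and limits the point. A reader might infer that the plan keeps the baseline out of the outcome model; the article does not say so. A reader might infer that prior use is known to be imbalanced; the article acknowledges selection only in general terms. Nor are the values available for every participant: "Claims data will only be provided for individuals insured by one of the participating statutory health insurers". A reader might also take pre/post correlations of 0.3, 0.5 or 0.6, compute 1/(1 − r²) − 1, and claim the equivalent of 10%, 33% or 56% more patients. That is not supported. The correlations would be assumed and marginal, not incremental to the covariates already used, and the formula is for independent observations in a linear model, not for matched, clustered counts and costs.

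What the reply does not answer is that the matching set is a stated choice, that matching is what the article relies on against selection bias, and that a relevant variable it already plans to measure is absent from that set.

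**Conclusion.** The point holds as an improvement to a stated method. The propensity score is specified with three variables, pre-stay utilisation is to be measured, and no use of it is described. Given the different routes by which the two groups are assembled, residual imbalance in prior use is plausible.

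The size is uncertain: an SE reduction of about 1 to 5% for an assumed incremental R² of 0.02 to 0.10, and about 13% for 0.25. It is most credible for the three secondary utilisation outcomes. For length of stay and readmission the argument is mainly about confounding, and its magnitude depends on an imbalance that the article neither reports nor predicts. The precision gain comes from the outcome model; adding a variable to the matching alone need not narrow any interval.

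**What to change.** In Statistical methods {20a}:

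1. Add pre-stay utilisation and earlier hospital stays to the propensity score.
2. Model each post-stay utilisation outcome with its own pre-stay value as a covariate in the GLMM/GEE.
3. Define the pre-stay window in advance so that it ends before the referral contact. Controls have no recorded STATAMED referral contact, so one workable form is a window ending a fixed number of days before admission, the same in all groups and long enough to cover the interval from case review to admission.

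The cost is wording, a little more analysis work and the decision on the window. Inpatient and outpatient claims are already in the data set (Table 1); the team should confirm that the extract reaches back far enough for earlier hospital stays. Data deliveries are planned for about June 2026 and January 2027, so the choice can be fixed before outcome data are seen if it is recorded before the first of these.
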